### Blood measures

Blood is drawn after an 8-h fast at baseline, 4-week, and 8-week study visits to perform several different assays.

At baseline, apolipoprotein E (APOE) genotype is determined using a TaqMan single-nucleotide polymorphism (SNP) allelic discrimination assay (ThermoFisher). APOE2, APOE3, and APOE4 alleles are determined using TaqMan probes at the two APOE-defining SNPs, rs429358 (C_3084793_20) and rs7412 (C_904973_10).

At baseline, 4 weeks, and 8 weeks, serum creatine is quantified via enzymatic assay (Quest Diagnostics). We expect serum creatine levels to increase as a result of the intervention, which can be used as an objective biomarker of compliance.

A comprehensive metabolic panel including liver and renal function tests (Quest Diagnostics) is measured at baseline and 8 weeks to monitor safety of the intervention.

Blood-based mitochondrial biomarkers are measured by the KU ADRC Biomarker Core at baseline and 8 weeks. Blood is collected into acid citrate dextrose tubes and fresh platelets, and lymphocytes are promptly isolated from the samples. Platelet and lymphocyte plasma membranes are permeabilized by adding digitonin, and the OROBOROS Oxygraph-2 k (OROBOROS Instruments, Austria) instrument is used to measure platelet and lymphocyte mitochondrial oxygen respiration kinetics. Reactive oxygen species (ROS) is measured using Amplex Red and MitoSOX with flow cytometry. ATP and ADP levels are measured using a bioluminescent assay.

### Muscle function and morphology

Muscle function is assessed at baseline and 8 weeks using handgrip strength and leg extensor strength testing. Handgrip strength is measured as the average of three consecutive tests with a hand dynamometer (Lafayette Instrument, USA) while seated in a chair with feet resting on the floor. The study team verbally encourages participants to squeeze the dynamometer with maximal effort for at least 3 s. Leg extensor strength is measured by completing five maximal isokinetic contractions of the right leg extensors at three different velocities (1.05 rad·s^−1^, 2.09 rad·s^−1^, and 3.14 rad·s^−1^) on a calibrated isokinetic dynamometer (Biodex Medical Systems, Inc., USA) [40]. Study personnel verbally encourage participants to work as hard and as fast as possible during each repetition. Torque, position, and velocity signals from leg extensor strength testing are recorded.

Muscle morphology is assessed at baseline and 8 weeks using ultrasonography (GE Healthcare UK, UK) to measure muscle cross-sectional area (mCSA) and echo intensity (mEI) of the right quadriceps muscles, while participants lie supine. All ultrasound imaging analyses are performed using ImageJ software (Version 1.46r, National Institutes of Health, Bethesda, MD, USA).

### Progression to a larger clinical trial

Meeting our primary feasibility goal of 80% compliance with the intervention protocol (*n* ≥ 16 participants that report consuming ≥ 80% of the CrM doses) will constitute a successful study, regarding feasibility. To support progression to a future randomized, controlled trial investigating differential effects of CrM and placebo on brain health outcomes in patients with AD will require both demonstration of feasibility and a positive signal from any of our secondary physiology or cognition outcomes. These measures were designed to generate preliminary data on symptoms and physiology that may be relevant to AD; thus, any changes associated with the CrM intervention would warrant broader, large-scale investigation.

## Data analysis

Demographic characteristics of study participants will be presented as means and standard deviations for continuous variables and frequencies and proportions for categorical variables.

The aim of this study is to determine feasibility of the CrM intervention and outcomes assessments in patients with AD. Our primary outcome will be compliance, which we consider compliance with the intervention among 80% of the study sample to be satisfactory. We will also use our recruitment tracking pipeline to determine the length of time required to enroll our full sample, the proportion of interested participants that consented to enroll in the study, and the reasons for non-recruitment, non-enrollment, and non-compliance.

We will also explore preliminary data regarding change in several AD-related secondary outcomes. Since all participants receive the CrM intervention, we will conduct paired samples *t*-tests for all outcomes to estimate means and 95% confidence intervals of within-group change from baseline. If model assumptions are not met, we will alternatively use the nonparametric paired Wilcoxon test to report medians and interquartile ranges. Statistical analyses will be performed using R (v. 4.2.1; R Foundation, Vienna, Austria).

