### Trial design

CABA is a single-arm, open-label, pre-post pilot trial. We will recruit 20 participants with AD, and all will be assigned to the 20 g/day CrM supplement intervention for 8 weeks. This dosage has been shown to be feasible and safe in healthy older adults, and limited data suggest that it may raise Cr levels in the brain [22].

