### Sample size

The primary aim of CABA is to investigate the feasibility of the CrM intervention; thus, formal estimates of power are not required [27]. This is the first human trial to investigate CrM supplementation in patients with AD. The secondary aims of CABA are designed to generate means and confidence estimates that inform sample size requirements of subsequent studies. With a sample size of 20, we will be able to estimate an 80% compliance rate with a 95% confidence interval of 62.5–97.5% and establish effect estimates and confidence intervals that can be used to inform the design of future large clinical trials.

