## Discussion

To date, the CABA study is the first to investigate CrM supplementation in patients with AD. Investigating CrM as an adjuvant therapy in AD is supported by recent positive animal studies and may influence several bioenergetic-related targets including mitochondrial function, oxidative stress, and inflammation. This pilot trial will provide information regarding the feasibility of the CrM intervention and the study outcomes, collectively, to inform the optimal design of a future clinical trial.

The CABA trial is not designed to determine efficacy of the CrM intervention in AD; thus, any results from its secondary outcomes should be interpreted with caution. The single-arm design of this study does not allow for comparison of change in secondary outcomes with a control group. This study also features a relatively small sample size along with measurement of several physiologic variables, which increases the chance for type I error due to multiplicity. However, since AD is a progressive disease, without intervention, we would expect either decline or no change in cognition from our participants. We also would not expect brain tCr levels or mitochondrial function to increase substantially with no intervention. Therefore, within-group signal for improvement in our secondary outcomes would provide further rationale for testing with larger studies. CABA is an important first step in generating effect estimates and confidence intervals to aid in determining the appropriate sample size necessary for hypothesis testing in a subsequent clinical trial.

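### The fallback for secondary outcomes reports a median and interquartile range, so outcomes that fail the assumption check are planned without the effect estimate and confidence interval that the secondary aims are meant to supply

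*Protocol article*

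**What the plan says.** The purpose of the secondary outcomes is stated three times in the protocol article.

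- Sample size: "The secondary aims of CABA are designed to generate means and confidence estimates that inform sample size requirements of subsequent studies".
- Sample size, as part of the case for 20 participants: the study will "establish effect estimates and confidence intervals that can be used to inform the design of future large clinical trials".
- Discussion: "CABA is an important first step in generating effect estimates and confidence intervals to aid in determining the appropriate sample size".

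The Data analysis section first gives an analysis that matches this purpose: "we will conduct paired samples *t*-tests for all outcomes to estimate means and 95% confidence intervals of within-group change from baseline". It then adds a conditional branch, opened by "If model assumptions are not met", in which "we will alternatively use the nonparametric paired Wilcoxon test to report medians and interquartile ranges". The branch is worded as a replacement for the t-test analysis and not as an addition to it. No criterion for entering it is given.

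**The concern.** The two branches do not deliver the same thing. The t-test branch gives a mean change and a 95% interval. The SD of change also follows from that interval and n. The fallback branch gives a median and an interquartile range, which summarise how participants differ from one another. They do not say how precisely the average change has been estimated.

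A pilot with no control arm and no power calculation has little to offer on its secondary outcomes beyond estimates and their precision, and the article says so. If the plan is followed as written, outcomes in the fallback branch are published without those estimates. They also cannot be set beside the other outcomes on a common scale. A reader planning a trial from the published report would have to guess the mean and SD of change from the median and interquartile range, in the very outcomes where such guesses are least reliable.

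**Working it through.** **1. The article's own precision figure.** Sample size states that "we will be able to estimate an 80% compliance rate with a 95% confidence interval of 62.5–97.5" per cent. With p = 0.80 and n = 20, the Wald interval is 0.80 ± 1.96 × √(0.80 × 0.20 / 20) = 0.80 ± 0.175, or 62.5% to 97.5%. The figure reproduces. The present point does not depend on it, but it shows that the authors think of precision in terms of confidence intervals.

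**2. What each branch delivers.**

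| Item | Paired t-test branch | Wilcoxon branch as written |
|---|---|---|
| Mean change | yes | no |
| 95% CI for change | yes | no |
| SD of change | recoverable: CI half-width × √n / t | no |
| Median and IQR | not needed | yes |

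The fallback sentence does not say whether the median is of the paired change or of the values at each visit. In the second case not even a summary of change would be reported.

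**3. IQR against confidence interval.** Assume n = 20 complete pairs (Trial design: "We will recruit 20 participants with AD, and all will be assigned to the 20 g/day CrM supplement intervention for 8 weeks") and normally distributed changes.

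- Width of the 95% CI for the mean: 2 × t(0.975, 19) / √20 = 2 × 2.093 / 4.472 = 0.936 SD.
- Width of the IQR: 2 × z(0.75) = 2 × 0.6745 = 1.349 SD.
- Ratio: 1.349 / 0.936 = 1.44.

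With 16 complete pairs the CI would be 2 × 2.131 / 4 = 1.07 SD wide, and the expected IQR would still be about 1.35 SD. The CI depends on n and the population IQR does not, so one cannot be read as the other.

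**4. Can the planning inputs be recovered from the IQR?** The usual back-calculation is SD ≈ IQR / 1.349. The article gives no SD or distribution for any outcome, so the distributions below are assumptions. They were simulated at n = 20. The second column is the typical (median) recovered SD divided by the true SD. The third is its square, because a sample size scales with SD².

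| Assumed distribution of changes | Recovered SD / true SD | Resulting N / required N |
|---|---|---|
| Normal | 0.92 | 0.84 |
| t with 3 df | 0.61 | 0.37 |
| Lognormal, log-SD 0.8 | 0.58 | 0.34 |
| Lognormal, log-SD 1.0 | 0.45 | 0.20 |

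In the two lognormal cases the mean and median also differ by about 0.3 SD. Recovery is fair when normality holds and poor when it does not, and the fallback is meant for the second situation.

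**5. Is an interval available in the fallback?** Yes. Inverting the signed-rank test at n = 20 (critical value 52) gives the Hodges-Lehmann interval from the 53rd to the 158th of the 20 × 21 / 2 = 210 ordered Walsh averages, with exact level 95.16%. Simulated coverage was 95.2% for both normal and t(3) changes. Mean width was 0.95 SD against 0.92 SD for the t interval under normality. Under t(3) it was 1.23 against 1.46, in units of the t(3) scale. The interval is feasible at this sample size and costs almost nothing in precision.

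**The case against.** **What stands on the other side.** The team keeps every paired value, so it can compute a mean, SD and interval for any outcome when it plans the next trial. The Dissemination section also promises analysis code and de-identified data on request. The loss is therefore in the planned report and not in the data, and it falls mainly on outside readers. It touches only outcomes that enter the fallback. These outcomes are exploratory, and the Discussion already advises caution in reading them. The Wilcoxon test is legitimate, and giving a median and IQR beside it is common practice.

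**What does not stand.** It can be argued that a condensed article leaves such detail to a fuller document. Here, however, the article states what the fallback will report, and that output does not match the purpose it states elsewhere. Nor does the opening commitment to means and intervals for all outcomes settle the matter, because the next sentence replaces it when assumptions fail.

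**Stronger readings a reader might infer, which the documents do not support.**

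- *Outcomes in the fallback cannot inform a sample size.* This is too strong, since the team holds the data.
- *Switching between tests gives each outcome a second chance of a signal.* The plan gives each outcome one test, not the better of two. If the check is assumed to be a 5% Shapiro-Wilk test, the simulated error rate of the switching rule at n = 20 stayed near 5% for normal and symmetric changes. For skewed changes with mean zero it was about 9 to 10%, against about 7% for the t-test alone. That is the rate of the Wilcoxon test used by itself, because it addresses a different null hypothesis.
- *A predictable number of outcomes will switch, or the switch is close to arbitrary.* The article names no formal pre-test, no significance level and no count of analysed variables, so any such figure would describe a procedure supplied by the reader.
- *The plan misstates what the signed-rank test tests.* It says only that medians will be reported with the test.

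**Conclusion.** The point holds as a mismatch between stated purpose and planned output, both in the article's own text. For any secondary outcome whose assumptions fail, the planned report omits the mean or effect estimate and the confidence interval that the Sample size and Discussion sections give as the reason for measuring it. The median and IQR do not replace them: at n = 20 with normal changes, an IQR of about 1.35 SD sits beside a 95% interval of about 0.94 SD, and the two measure different things. The back-calculation results show how far planning inputs could drift, but they rest on assumed distributions and are illustrations only.

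The weight is minor to moderate. The number of outcomes affected is unknown, the omission can be repaired from the retained data, and the primary compliance outcome is not touched.

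**What to change.** Replace the fallback sentence in Data analysis with a rule of this kind: for every secondary outcome, report the mean paired change, the SD of change and the 95% confidence interval; where the assumptions of the t interval are in doubt, add the Hodges-Lehmann estimate of the paired change with its 95% confidence interval, or a bootstrap interval for the mean change; give the median and interquartile range of the paired change only as further description.

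The article already names R, where the Hodges-Lehmann interval comes from `wilcox.test` with `paired=TRUE` and `conf.int=TRUE`. With skewed changes the Hodges-Lehmann estimate does not target the mean, so it should accompany the mean and SD and not take their place.

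The cost is slightly more output per outcome. No new data, visits or participants are needed, and the Wilcoxon test itself can stay.

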## Data management and security

Data is collected both on paper and electronically. All paper data are stored securely in a locked filing cabinet at KUMC. All electronic data is managed using the Research Electronic Data Capture (REDCap) [41, 42] system hosted by a HIPAA-complaint server. Data is entered by the research staff and validated with real-time entry validation and offline validation by the investigators. The study team is assigned role-based access to REDCap which is protected by institutional multi-factor password protection.

All data is gathered for the explicit purposes of this study using procedures to ensure confidentiality. Within the REDCap database, participant identifiers are available to the study interventionalists only as they will be responsible for participant scheduling and delivery of the intervention. For all other study investigators, all data is de-identified and organized by participants’ assigned study IDs only. All data for publication or presentation will also be deidentified.

## Dissemination

The results of this study will be published in peer-reviewed scientific journals and will be presented at international conferences, such as the Alzheimer’s Association’s International Conference. The research team will agree upon authorship in advance of manuscript submission. We will include statistical code used for data analyses as supplemental data with submitted manuscripts. Final de-identified data will available upon request to the principal investigator, contingent upon completion of a data sharing agreement with the University of Kansas Medical Center.

## Discussion

To date, the CABA study is the first to investigate CrM supplementation in patients with AD. Investigating CrM as an adjuvant therapy in AD is supported by recent positive animal studies and may influence several bioenergetic-related targets including mitochondrial function, oxidative stress, and inflammation. This pilot trial will provide information regarding the feasibility of the CrM intervention and the study outcomes, collectively, to inform the optimal design of a future clinical trial.

The CABA trial is not designed to determine efficacy of the CrM intervention in AD; thus, any results from its secondary outcomes should be interpreted with caution. The single-arm design of this study does not allow for comparison of change in secondary outcomes with a control group. This study also features a relatively small sample size along with measurement of several physiologic variables, which increases the chance for type I error due to multiplicity. However, since AD is a progressive disease, without intervention, we would expect either decline or no change in cognition from our participants. We also would not expect brain tCr levels or mitochondrial function to increase substantially with no intervention. Therefore, within-group signal for improvement in our secondary outcomes would provide further rationale for testing with larger studies. CABA is an important first step in generating effect estimates and confidence intervals to aid in determining the appropriate sample size necessary for hypothesis testing in a subsequent clinical trial.

## Trial status

This manuscript reflects protocol version 2 dated March 17, 2023. Recruitment began in December 2022. We anticipate completion of all trial assessments by the end of June 2024.

## Data Availability

Not applicable. No datasets were generated or analyzed.

## Abbreviations

AD: Alzheimer’s disease
AE: Adverse event
APOE: Apolipoprotein E
ATP: Adenosine triphosphate
BB-CK: Creatine kinase brain isoenzyme
BMI: Body mass index
CABA: Creatine to Augment Bioenergetics in Alzheimer’s disease
CBF: Cerebral blood flow
Cr: Creatine
CrM: Creatine monohydrate
DHQ III: Diet History Questionnaire III
GSH: Glutathione
mCSA: Muscle cross-sectional area
mEI: Muscle echo intensity
MMSE: Mini-mental state exam
MRI: Magnetic resonance imaging
MRS: Magnetic resonance spectroscopy
NAA: N-Acetylaspartate
NIH-TB: NIH Toolbox®
PCr: Phosphocreatine
tCr: Total creatine
